### Ethical considerations

The study was approved by the Ethics Committee of Hamadan University of Medical Sciences with Proprietary ID: IR.UMSHA.REC.1395.435 and agreed by Isfahan University of Medical Sciences (administrators at the research sites). For couples who voluntarily apply for study,the objective and process of the study will be described in detail and fully before entering the study, and the couples can decide whether to enter the study with this information or not. In the informed written consent form that the volunteers must carefully study and sign on before entering the study, it will be stipulated that the content of the study and questions is about your private matters that might be matter of concern. They will be assured that their personal information will not be disclosed at all, their statements will remain confidential and only the research team will have access to it. The actual name of the participants will not be requested at any stage of the study. Participants will be assigned a code that will be identified by the code until the end of the study. It is also emphasized that entry into the study is completely voluntary and participants who are uncomfortable with the sensitivity of the content or questions can be excluded at any stage of the study without any conditions. Due to the sensitivity of the questions, data collection will be done online, and unnamed answer sheet of participants will only be visible to the main investigator so that the participants do not feel uneasy about sharing their answers with other members of the health center that they are referring to. The time of workshops will be determined by the participants and will be considered an appropriate place for holding workshops to provide easy access to all participants. The contents of the book and workshops and messages have been based on the couple’s statements in the qualitative stages and the results of cross-sectional stage, in order to be completely in line with the needs and indigenous religious and cultural values and norms of spouses and do not conflict with them. Only research team members will have access to collected data. The data file will be stored on a secure server with a password, which will be provided only to the research team members.

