#### Description of intervention

The training package of enrichment of couples’ sexual interactions were designed based on the content of individual interviews with 22 couples in the qualitative phase and the results of the cross-sectional phase of study (*n* = 400) and according to the IMB model. This package includes the 18-h Marital and Sexual Skills Training Workshop, the presentation of the “My Soul Partner” book which is given to each couple for free and sending short messages.

The “My Soul Partner” book is written by second author who is **sexo**logist. The aim of this book is skill training of intimate and sexual relationships of couples in the form of religious and cultural values and norms of the Iranian community that empower couples to have a healthy and intimate marital life. The book forms the educational content of the workshop, which includes the topics of the effective communications of spouses, the anatomy and performance of reproductive organs, the vocabulary and patterns of human sexual response, the sexual communication skills, sexual relationships during pregnancy, sexual health and sexual problems. The content will be presented using collaborative approaches such as, the group discussion, role playing and question and answer in the workshop, and the couples will solve the exercises and self-tests in the book and discuss the results. The 18-h workshop will be planned in the form of six 3-h workshop in 6 consecutive weeks that will be considered rest and catering among meeting sessions for participants. The location of workshops will be at one of the health centers in the center of the city. It is convenient to move all participants from different parts of the city at this central location. The time of holding the workshop will be determined by the participants and will be tried in a way that does not interfere with the working hours of the participants. Teaching in workshops will be handled by two people from the research team.

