#### Description of the control

Couples in control group will not receive an intervention after completing the baseline questionnaire, and receive only the reproductive health care provided at the urban health centers. The services provided by the family and community health unit in urban health centers for couples include family planning, counseling and treatment for STDs and HIV/AIDS, premarital training, counseling and screening for reproductive system cancers including breast and cervical cancer. But there is no service in the field of sexual health. Couples in two groups receive routine services.

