#### Outcome assessment

The outcomes will be measured through the online individual, close ended questionnaire, which is designed on Google Form (https://docs.google.com/forms) and its link will be sent to mobile phone’ participants via accessible social networks (Telegram, WhatsApp messenger, Instagram, IMO and LinkedIn). Given the confidentiality of the questions, this method has been chosen to enhance the privacy of participants and feel more comfortable in answering the questions. Only the main investigator will be able to view the responses. The questionnaires will be administered at the baseline (before assigning couples to the study arms) and 4 months after the end of the intervention. To evaluate the primary outcomes, the SIMBS questionnaire will be used which was designed by the research team based on individual interviews with couples and according to the IMB model and its psychometric properties were confirmed in 200 couples (*n* = 400). To evaluate the secondary outcome, Larson’s Sexual Satisfaction Questionnaire [24] will be used, whose validity and reliability has been confirmed in Iranian couples [8]. The main investigator will contact the couples at the baseline and four months after the intervention and explain how they will fill the questionnaire. This description will be sent in writing along with the questionnaire and instructions for completing the questionnaire. Also, a phone number will be given to couple to contact the research team if they have any questions. Then the questionnaire link will be sent to them. All participants will send their responses via mobile phone. The proper security measures will be taken to assured and arcane transfer data to a secure database.

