### Follow up and data collection

After the workshops, the couples will be followed for 4 months. During this time, they will be asked to read the “My Soul Partner” book carefully with their spouse and complete the exercises and talk about the results together. Also short messages in the field of skill training for sexual relationship will be sent to them by cell phone. Short messages will be based on the content of the book and workshops, which will be sent to recall and review the submitted content. These messages will be transmitted through the creation of a telegram group, which all couples in the intervention group will be members of, and sent as a message every week. Couples will also be able to ask questions about the content of the book and workshops, from the administrators of the group who will be a member of the research team and will provide an answer within 48 h. Data will be collected at the baseline and at four months after the intervention. The original researcher will contact the participants at baseline and at 4 month after the intervention and will coordinate with them to send the questionnaire link. Participants will be asked to respond and submit their responses within a week. If they do not reply within a week, they will be contacted three times. In case of non-response after three times, they will be excluded from the study.

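### The exit provision ties discomfort with the study content to leaving the study and offers no way to stop the package while staying in follow-up, which risks extra, probably informative, loss in the intervention arm

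*Protocol article*

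**What the plan says.** The exit provision is in the protocol article under Ethical considerations: "participants who are uncomfortable with the sensitivity of the content or questions can be excluded at any stage of the study without any conditions". The Recruitment section adds a general right to withdraw from the study. Neither place separates stopping the training from ending data collection.

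The word *content* is used in two ways in that section. In the consent wording for all volunteers it refers to the study as a whole: "the content of the study and questions is about your private matters that might be matter of concern". Later it refers to the training material: "The contents of the book and workshops and messages have been based on the couple’s statements".

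The arms differ in what they are exposed to:

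- **Intervention arm.** Description of intervention states: "This package includes the 18-h Marital and Sexual Skills Training Workshop, the presentation of the “My Soul Partner” book", together with short messages. Follow up and data collection describes a Telegram group "which all couples in the intervention group will be members of, and sent as a message every week".
- **Control arm.** Description of the control states: "Couples in control group will not receive an intervention after completing the baseline questionnaire". Routine care continues.
- **Both arms.** Outcome assessment states: "The questionnaires will be administered at the baseline (before assigning couples to the study arms) and 4 months after the end of the intervention".

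On timing, Follow up and data collection says: "After the workshops, the couples will be followed for 4 months". The same section drops people who do not answer after three contacts, in either arm.

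**The concern.** Someone who finds the workshop material uncomfortable is told of one remedy, which is to leave the study. Some of these people might have answered an online questionnaire four months after the workshops if they had been offered a lesser option. Their outcomes are then lost unnecessarily, and no analysis plan can recover a questionnaire that was never sent.

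The loss is unlikely to be neutral. The Background describes a belief that talking about sex is sinful and links it to poorer sexual relations between spouses, and the Discussion refers to conservative cultural and religious beliefs. Attitude towards sexual relations is itself part of the primary outcome. People who leave over the material therefore plausibly differ on what is being measured. If more of them leave the intervention arm, its 4-month mean describes couples who tolerated the package, and the comparison moves in the package's favour. The Discussion intends the result to inform national implementation, where acceptability to all couples matters.

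**Working it through.** **Step 1: which exits can occur in which arm**

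| Reason for exit | Intervention | Control |
|---|---|---|
| Discomfort with the questions | yes | yes |
| Discomfort with the study as a whole | yes | yes |
| Discomfort with workshop, book or messages | yes | not applicable |
| General withdrawal | yes | yes |
| Non-response after three contacts | yes | yes |

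The intervention arm has one additional route. The others are shared.

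**Step 2: the plan's own figure**

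The only loss rate in the article is the 5% under Sample size, given with 80% power, alpha 0.05, a difference of 5.38 points in sexual satisfaction and a total of 200 people. No SD is given, so 200 can be neither confirmed nor refuted. Working backwards with a two-sided test and people treated as independent, an SD of about 13.2 gives 95 per arm, 95/0.95 = 100 after loss, and 200 in total. An SD of 12 gives 168 and an SD of 14 gives 226.

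**Step 3: power is not the main issue**

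With an SD of 13.24, 100 people per arm and loss in the intervention arm only, power is 82.0% with no loss, 81.0% at 5%, 79.9% at 10% and 77.3% at 20%.

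**Step 4: bias**

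Let p be the share of an arm lost and g the mean of stayers minus the mean of leavers. The stayers' mean exceeds the full-arm mean by p × g, so:

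bias = p(intervention) × g(intervention) − p(control) × g(control)

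The article gives no p by arm and no g. All values below are assumptions.

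- *Leavers gain none of the 5.38 points, and the extra loss is in the intervention arm only.* 0.05 × 5.38 = 0.27 and 0.20 × 5.38 = 1.08 points, that is 5% to 20% of 5.38.
- *Gap in SD units (SD 13.24), 10% extra loss.* 0.10 × 0.5 × 13.24 = 0.66 points (12% of 5.38), and 0.10 × 1 × 13.24 = 1.32 points (25%). With no true effect, the two-sided type I error would be 6.4% and 10.6%.
- *Loss in both arms, 10% against 5%, same gap of 0.5 to 1 SD.* (0.10 − 0.05) × 6.62 = 0.33 and (0.10 − 0.05) × 13.24 = 0.66 points, half of the one-arm values.
- *Equal loss and equal gap.* Bias = 0.

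**Step 5: couple scores**

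Statistical analysis merges the male and female satisfaction scores into one, so the exit of one spouse can cost the couple's score. If 10% of individuals left independently (assumed), 1 − 0.90² = 19% of couples would lack a complete pair; if spouses always left together, 10% would.

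**The case against.** A reader might infer that stopping the package automatically removes a couple's outcomes, and that this can happen in one arm only. The document does not support that:

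- The sentence is permissive. It sets out a consent right and does not require anyone to be removed.
- Its trigger covers the questions as well as the content, and both arms answer the questions.
- *Content* is used first for the study as a whole, so a control participant can invoke the provision too.
- Outcome assessment and Follow up and data collection set no attendance condition for the questionnaire. The statement "After the workshops, the couples will be followed for 4 months" gives timing. A couple who miss sessions without asking to leave would, on this text, still be contacted.

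All of this stands. It is also fair that the bias figures rest on assumed inputs, and that 5.38 belongs to the secondary outcome; the article gives no figure from which to size the effect on the primary scores. If the planned ANCOVA adjusts for baseline (its covariates are not named), it would remove part of any gap due to a lower starting score, though not a gap due to leavers failing to gain.

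One could add that an article may leave the distinction between stopping training and ending follow-up to a fuller protocol. That limits the weight of the point but does not remove it. The article does state an exit provision, and what it states offers only departure from the study.

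**Conclusion.** The point holds in a limited form. Discomfort is tied to leaving the study, with no stated option to stop the package and remain in follow-up. Because the workshop, book and messages exist in one arm, this can produce additional and probably informative loss there, on top of exits that both arms share. Automatic removal of outcomes, or loss confined to one arm, is not established.

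The size is unknown. The illustrative inflation of 0.27-1.08 points assumes 5-20% extra loss in the intervention arm and a gap of 5.38 points between stayers and leavers. It shrinks as control losses with a similar gap approach those of the intervention arm, and it is zero when loss and gap are equal. The stated sample size does not change. This is an inexpensive improvement in data collection and not a flaw that undermines the design.

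**What to change.** In Recruitment, Follow up and data collection, and Ethical considerations, and in the matching consent text, state that:

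1. A participant may stop sessions, book or messages without leaving the study.
2. That person will still be offered the 4-month questionnaire on the same calendar schedule as the rest of the arm, and will be analysed in the arm allocated.
3. The right to withdraw from the whole study, at any point and unconditionally, is unchanged. The new option is an offer and adds no condition to leaving.
4. For each type of exit the arm is recorded, with the reason where the participant volunteers it.

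The cost is a short edit in three sections and the consent text, plus a little more follow-up contact; the online link and the contact process already exist. The effect estimate may come out smaller, because it would include people who did not complete the package.

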## Discussion

One of the factors that affects couple’s sexual satisfaction is their familiarity with sexual issue [13]. Sex education includes learning about sexuality, sex, relationships, emotions, creating positive beliefs, values and attitudes [25], which helps couples to have more rational and responsible sexual relationship and prevent sexual dysfunction [14]. In spite of the relatively high level of literacy in Iran that paves the way for educational programs, the existence of a highly effective and efficient primary health care system [26], family planning and national programs for reproductive health of youth [27], the issue of sexual skills training is not adequately addressed. The conservative cultural and religious beliefs of society have led to a lack of valid educational materials and the shift of young people to satellite and pornographic products to meet their sexual needs [28]. The results of the qualitative phase of the present study showed that the participating couples did not have enough information on sexual issues. Many interventions have been designed to promote sexual health of young people in the world that few of them have been successful [29]. Some scholars view the failure of these interventions, the lack of attention to causal studies and their planning without considering psychosocial models as a specific framework [30]. In this study, qualitative study was carried out to identify the factors affecting sexual satisfaction of couples. Accordingly, the IMB model was selected for intervention planning. This model has been used in many sexual health interventions and often used to reduce risky sexual behaviors lead to HIV/AIDS [31–33]. One of the innovations of current study is to use the IMB model to promote healthy sexual behaviors of couples. Interventions are planned based on the results of qualitative and quantitative phase of study tailored to the values and norms governing the sexual life of Iranian couples. Interactive methods will be used to provide educational interventions that will lead to more engaging couples in the subject. Recently, interest has been given to trials that can be done completely or partially over the Internet [34]. The Internet live stats statistical site is estimated the number of Internet users in Iran in 2016 at 39 million [35]. According to the Ministry of Communications, more than 92% of Iranians have mobile phones, and 65% of them are members of one of the social networks, with more than 40 million telegram users in Iran. Therefore, in this study, social networks will be used for recruitment of participants, the measurement of the outcomes of study and the sending educational messages in the follow-up period. Online recruitment of participants may cause unrepresentative sampling; on the other hand, all eligible couples do not go to health centers. Therefore, both call methods through health centers and online call on social networks will be used for sampling so that the maximum numbers of eligible couples have the chance to enter the study. Using the online method to measure the outcomes of the study, while enhancing the confidentiality of the participants, can lead to a decline due to the lack of response from some of the participants. In these cases, it is anticipated that three times a phone call will be conducted by members of the research team and engagement of the couples. In this trial, the impact of the sexual relationship enrichment package on sexual satisfaction of couples will be examined. If the trial is effective, its results will be presented to policy makers for implementation at national level.

## Data Availability

The data that support the findings of this study are available from [name] but restrictions apply to the availability of these data, which were used under license for the current study, and so are not publicly available. Data are however available from the authors upon reasonable request and with permission of Ethics Committee of Hamadan University of Medical Sciences.

## Abbreviations

IMB: Information, motivation and behavioral skills model
IMO: In My Opinion
SIMBS: Sexual information, motivation and behavioral skills scale
